For primary safety endpoint, estimates by anticoagulant treatment and for both populations (anticoagulant‐naive and anticoagulant‐experienced patients) will be addressed by using the same methods as described for the primary effectiveness endpoint.

In order to account for confounding in the comparative analyses, several methods will be performed to compare groups of patients with the similar characteristics including: adjustment on propensity score (estimation of the average treatment effect in the entire population if the treatment might be offered to every member of the population, ATE), matching on propensity score (estimation of the average treatment effect of matched subjects who ultimately received the treatment, ATT), and two other comparative approaches as sensitivity analyses (using high dimensional propensity scores, and adjustment on confounders).

The main method will consist in propensity score adjustment to compare groups of patients with the same characteristics. The propensity score is the probability of treatment assignment conditional on observed baseline characteristics. Propensity score is used when selection bias due to non‐random treatment assignment is likely, because of observational data. Three different propensity scores will be performed according to the comparison (apixaban vs dabigatran, apixaban vs rivaroxaban or apixaban vs VKAs). The propensity score conventional method will be used, which is to derive a score based on all the confounding factors previously identified. The probability to be treated with a given therapeutic combination will be estimated using a logistic regression model (with all confounding factors and treatment as dependent variable). Several checks will be performed to ensure a good balance of propensity score and of covariates between apixaban and comparison groups:First, the treatment group propensity score distribution will be analyzed with a graphical representation. If no overlap between distributions is observed, patients will be defined as different, so comparisons would not be performed.Then, the balance of propensity score across treatment and comparison groups will be checked, with comparison of means. The balance of covariates across treatment and comparison groups will be checked using standardized difference.^17^

If no balance, a new propensity score model will be specified (deletion of variables or transforms).^17^

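### If balance is not reached, the plan allows variables to be deleted from a propensity score meant to hold all identified confounders, which leaves a deleted confounder unadjusted in the main comparative analysis

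*Protocol article*

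**What the plan says.** All of this is in section 3.4.1 of the protocol article.

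- **Main comparative method.** "The main method will consist in propensity score adjustment to compare groups of patients with the same characteristics". Matching on the score is also planned. A high-dimensional score and direct adjustment on confounders are sensitivity analyses.
- **Content of the score.** The instruction is to "derive a score based on all the confounding factors previously identified", by logistic regression, separately for each of the three apixaban comparisons.
- **Checks.** The score distributions are first inspected for overlap. Next, "the balance of propensity score across treatment and comparison groups will be checked, with comparison of means". Last, "The balance of covariates across treatment and comparison groups will be checked using standardized difference". The article does not say whether the means are compared in the unadjusted groups, within score strata or after matching. It also does not say whether a variable dropped from the score stays in the covariate check.
- **Remedy.** "If no balance, a new propensity score model will be specified (deletion of variables or transforms"). No variable is protected from deletion.

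Section 2 lists the comparisons with apixaban as a secondary objective, in anticoagulant-naive patients only.

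**The concern.** Two instructions in the same section conflict. One puts every identified confounder in the score; the other lets variables be taken out when balance is not reached. Since the candidates are confounders by selection, deletion does not cure an imbalance. It only stops the main analysis from adjusting for it.

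The check on score means can push in the same direction. Adjustment on the score creates no matched or weighted sample in which mean scores ought to agree. If the raw groups are compared, a score that captures strong prescribing preferences fails the check, and removing the strongest predictors of treatment is the easiest way to pass.

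At stake are the adjusted comparisons of apixaban with VKAs, dabigatran and rivaroxaban. The introduction says that the health authority asked for data on apixaban compared with these treatments. The discussion relies on a large number of covariates to stand in for risk factors missing from the database, and deletion weakens that defence.

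**Working it through.** The article states no figure on this point, so there is none to reproduce. Steps 1 and 2 are algebra with an illustration. All numerical inputs in steps 1 to 4 are assumptions, not figures from the article.

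**Step 1. Raw score means differ whenever the score predicts treatment.** Let e be the true score and p = E[e] the proportion treated. Then E[e | treated] = E[e²]/p and E[e | untreated] = (p − E[e²])/(1 − p), so

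difference = Var(e) / [p(1 − p)].

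This is zero only if e is constant. Assume logit(e) = −0.3 + bX with X standard normal, integrated numerically:

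| b | p | Var(e) | Difference in mean score |
|---|---|---|---|
| 0.8 | 0.435 | 0.030 | 0.12 |
| 1.0 | 0.438 | 0.042 | 0.17 |
| 1.5 | 0.447 | 0.072 | 0.29 |

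**Step 2. Deletion moves the means together.** A score on fewer covariates is the conditional mean of the fuller score given those covariates. Its variance cannot be larger, while p is unchanged. By step 1 the gap in raw means shrinks or stays the same. The deleted confounder is no better balanced.

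**Step 3. Simulation.** Assumed inputs: 400,000 patients; two independent standard-normal confounders x1 and x2; treatment log odds ratio 0.2 for x1 and 0.3, 0.6 or 1.0 for x2; baseline rate 0.02 per year over one year; log hazard ratio 0.3 for x1 and 0.3 or 0.5 for x2; true rate ratio 1. The outcome was analysed by Poisson regression adjusted for 20 score strata.

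| Quantity, over six scenarios | Full score | x2 deleted |
|---|---|---|
| Standardized difference of the score, raw groups | 0.35 to 0.93 | 0.16 to 0.20 |
| Standardized difference of x1 within strata | 0.003 to 0.004 | 0.003 to 0.004 |
| Standardized difference of x2 within strata | 0.005 to 0.016 | 0.30 to 0.91 |
| Adjusted rate ratio (truth 1) | 0.98 to 1.07 | 1.11 to 1.58 |

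Scenario by scenario, deletion moved the rate ratio from 1.02 to 1.11, 1.02 to 1.18, 0.99 to 1.17, 0.98 to 1.29, 1.00 to 1.29 and 1.07 to 1.58. The score means drew together while the omitted confounder stayed imbalanced. A balance table listing only x1 would pass; one that kept x2 would not.

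**Step 4. A simpler bias figure.** For one unadjusted binary confounder with hazard ratio HR and prevalences p1 and p0, the spurious rate ratio is [1 + p1(HR − 1)] / [1 + p0(HR − 1)]. Assume p0 = 0.30 and HR = 2.

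- Odds ratio 1.5 between arms: odds 0.30/0.70 × 1.5 = 0.643, p1 = 0.391, ratio 1.391/1.30 = 1.07.
- Odds ratio 2: odds 0.857, p1 = 0.462, ratio 1.462/1.30 = 1.12.

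**The case against.** A reader might infer that confounders can be removed until the whole balance assessment passes. The article does not support that. A covariate's raw standardized difference does not depend on the score model, so deletion cannot improve it. Within strata or after matching, a deleted confounder would show as imbalanced. It is hidden only if it also leaves the balance table, and the article does not say that it does. This part of the objection stands.

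A reader might also infer that the comparison of means is certainly wrong. It is wrong as a pass criterion if made in unadjusted groups. Matching is planned too, and comparing score means after matching is sensible. A condensed article may leave that detail to the analysis plan, so the criticism of this check is conditional. The deletion rule is faulty under either reading.

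The rule also offers transforms, which are unobjectionable, and some deletions may be harmless where variables are redundant. Direct adjustment and the high-dimensional score could reveal a harmful deletion. These points lower the severity. They do not protect the main estimate, because the rule does not confine deletion to redundant variables and those two analyses are only sensitivity analyses.

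The overlap rule, which acts when no overlap is seen, is a separate matter. Handling of partial overlap is commonly left to an analysis plan and forms no part of this point.

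Finally, the sizes are wholly assumed. The step 4 figures suppose that no retained covariate acts as a proxy for the deleted one, and the simulation makes its two confounders independent. The full-score simulation itself reached 1.07 when the truth was 1, which equals the lower step 4 figure.

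**Conclusion.** The point holds in a limited form. The article requires all identified confounders in the score and then permits their deletion, so its own rule can leave a confounder unadjusted in the main comparative analysis. A comparison of raw score means would favour such a deletion; the covariate check would expose it only if the deleted variable is still tabulated.

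The direction of the fault follows from algebra. The size does not: 1.07 to 1.12 for one confounder, and 1.11 to 1.58 in the simulation, are illustrations on assumed inputs, not estimates for this study. The rule is contingent on a failed balance check and affects secondary comparisons in naive patients. The primary objectives, met by unadjusted estimates for each treatment, are unaffected. This should be fixed, but it does not undermine the study.

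**What to change.** 1. Remove deletion as a remedy for identified confounders. Respecify the score only by transforms, splines or interactions, and without looking at outcomes.
2. Judge balance by standardized differences on the full prespecified confounder list, whatever the final form of the score. For the main method, assess them conditional on the score, for example within score strata; for matching, in the matched sample. Checking only a matched or weighted sample would not do, because the main method produces neither and inverse probability weighting is mentioned in the discussion only as a possible future analysis.
3. Put any covariate that remains imbalanced in the outcome model.
4. Do not use equality of raw score means as a pass criterion.

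The cost is a change of wording and a little programming for the within-stratum balance table. No new data are needed and no patients are lost.

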#### Secondary outcomes

3.4.2

For the secondary outcomes, the comparison between patients initiating apixaban and patients initiating each of the other anticoagulant treatments (dabigatran, rivaroxaban, and VKAs) will be performed only in the four sub‐cohorts of anticoagulant‐naive patients.

For all other descriptive objectives, the analyses will be performed in the eight sub‐cohorts.

Estimation by anticoagulant treatment and for both populations (anticoagulant‐naive and anticoagulant‐experienced patients) as follows:Quantitative variables will be described with the sample size, mean, standard deviation, median, interquartile range, minimum and maximum.Qualitative and ordinal variables will be described with the sample size and frequencies.

Analyses in anticoagulant‐naive and anticoagulant‐experienced populations as follows:The major characteristics of patients will be described for each anticoagulant treatment.Treatment patterns at anticoagulant initiation, over time, and concomitant treatment will be tabulated by anticoagulant treatment.Time‐to‐discontinuation will be estimated and plotted using cumulative incidence function by anticoagulant treatment.Healthcare resources utilization will be described by anticoagulant treatment.

For each endpoint of interest in the study, only the first evidence of its event will be considered in the analyses. Cox models have been chosen to align with the methodology used in other OAC publications. As this study has been conducted to address a specific request from French health authorities, the comparability of the methods with other OAC publication was an important contributor of the analytical choices made a priori.

Cox models or Fine Gray models are planned to be used in the analyses. The final choice of model will be based on the observed death rates, that is, in case of a high likelihood of competing risk of death, Fine Gray models will be used rather than Cox models.

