#### Primary effectiveness and safety outcomes

3.4.1

For primary effectiveness outcome, estimates by anticoagulant treatment and for both populations (anticoagulant‐naive and anticoagulant‐experienced patients) of:The number and percentage of patients presenting at least a stroke and/or a systemic embolic event during the 12 months after index date, and during the overall follow‐up period. This description will be also conducted by diagnoses sub‐division presented in Table 1.The unadjusted incidence rate: number of first event of stroke and/or systemic embolism by 100 person‐years and during the overall follow‐up period will be estimated by anticoagulant treatment. Person‐years are defined with the sum of follow‐up durations of the at‐risk population. The corresponding two‐sided 95% CI will also be represented using Poisson distribution.The time‐to‐event of first occurrence of stroke and/or systemic thromboembolism will be estimated and plotted using cumulative incidence function (the cumulative probability of failure from a specific cause over time) accounting for differences in follow‐up time and the competing risk of mortality (if mortality is greater than 10%). In the presence of competing risks of mortality, informative censoring of the observation time at death will be used, as mortality will be considered a competing risk for observing stroke and systemic thromboembolic events since patients who die before an event is observed cannot go on to have an event. In the absence of competing risks, the differences in follow‐up time will be accounted for through non‐informative censoring of the observation time at the end of follow‐up for each patient. Overall, the causes of censoring of each treatment group will be reported once the results will become available. Cumulative incidence curves will present the event risk over time (within first 12 months) for each newly initiated anticoagulant treatment while accounting for the competing risk of mortality (if needed) and differences in follow‐up time.Median duration to occurrence of first event of stroke and/or systemic thromboembolism: median duration (in days) between the index date and the date of the first studied event will be computed for patients with the event.

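### Observed mortality decides between Cox and Fine-Gray for the apixaban comparisons, and between two estimators for the incidence curves; both should be fixed in advance, though the likely distortion is small

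*Protocol article*

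**What the plan says.** Section 3.4.2 (Secondary outcomes) covers the comparisons of apixaban with dabigatran, rivaroxaban and VKAs, which are confined to anticoagulant-naive patients. It makes two statements about the model, one after the other:

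- Cox is presented as settled: "Cox models have been chosen to align with the methodology used in other OAC publications". Comparability with those publications "was an important contributor of the analytical choices made a priori".
- The choice is then reopened: "The final choice of model will be based on the observed death rates", and "in case of a high likelihood of competing risk of death, Fine Gray models will be used rather than Cox models". No figure defines the trigger.

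Section 3.4.1 (Primary effectiveness and safety outcomes) has a second mortality rule, for the cumulative incidence curves. They account for "the competing risk of mortality (if mortality is greater than 10" per cent); otherwise observation is censored non-informatively at the end of each patient's follow-up, which includes death. The reason given for treating death as competing is that "patients who die before an event is observed cannot go on to have an event". The curves cover the first 12 months. Section 3.4.1 applies the same methods to major bleeding.

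**The concern.** Cox regression with deaths censored estimates the cause-specific hazard ratio: the relative event rate among patients still alive and event-free. Fine-Gray estimates the subdistribution hazard ratio, which describes cumulative incidence and keeps patients who have died in the risk set. Which one is wanted depends on the question asked, not on how many patients die. If observed mortality decides, the quantity reported is unknown until the data are in.

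The choice has consequences. Where two drugs have the same effect on stroke or bleeding but their users die at different rates, Fine-Gray gives a ratio away from 1, in favour of the group with more deaths. Unequal mortality is plausible: the Discussion expects VKA and NOAC users to differ in characteristics and comorbidities. A switch to Fine-Gray would also give up the comparability with other publications that the plan cites as its reason for Cox.

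For the curves, the plan's own reason for treating death as competing is true at any level of mortality, so a 10% threshold does not follow from it.

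**Working it through.** **Inputs.** The article gives no event rates, death rates or sample size. Its only figure on this point is the 10% threshold, so there is no calculation of its own to reproduce. Assumed here: constant hazards, stroke/systemic embolism rate l = 0.02 per person-year in both arms (no drug effect), and a range of death rates d.

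**1. Fine-Gray with no true stroke effect, complete follow-up.** Cumulative incidence is CIF(t) = l/(l+d) × (1 − exp(−(l+d)t)). The cumulative subdistribution ratio is ln(1 − CIF_low) / ln(1 − CIF_high), where low and high refer to mortality.

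Example at 1 year, deaths 5 vs 12 per 100 person-years: CIF_low = 0.02/0.07 × (1 − e^−0.07) = 0.01932; CIF_high = 0.02/0.14 × (1 − e^−0.14) = 0.01866; ratio 1.035.

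| Deaths per 100 person-years | 1 year | 2 years | 3 years |
|---|---|---|---|
| 5 vs 6 | 1.005 | 1.010 | 1.015 |
| 6 vs 9 | 1.015 | 1.030 | 1.045 |
| 5 vs 12 | 1.035 | 1.071 | 1.108 |

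The cause-specific hazard ratio is 1.00 in every cell.

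**2. Simulation check.** One data set of 100,000 per arm, 3 years of complete follow-up, deaths 5 vs 10 per 100 person-years, higher-mortality arm against lower: Cox 0.997 (95% CI 0.960–1.036), Fine-Gray 0.928 (0.893–0.964). The inverse of 0.928 is 1.078, against 1.076 from the formula in step 1.

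**3. Follow-up closer to the plan.** Under section 3.1, patients enter over 2014–2016 and leave at switch or discontinuation. The Fine-Gray score equation was solved with uniform entry over 3 years, the study assumed to end in December 2016, and stopping at 30–50 per 100 person-years. The censoring survival function is then (1 − t/3) × exp(−st), with s from 0.3 to 0.5.

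| Deaths per 100 person-years | Spurious ratio |
|---|---|
| 5 vs 6 | about 1.008 |
| 6 vs 9 | 1.023–1.025 |
| 5 vs 12 | 1.05–1.06 |

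**4. A true effect is distorted too.** A true cause-specific ratio of 0.80, where the better arm also has half the deaths (5 vs 10 per 100 person-years), becomes 0.82 at 1 year and 0.86 at 3 years under Fine-Gray with complete follow-up.

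**5. Curves below the 10% threshold.** Censoring deaths estimates 1 − exp(−l) at 12 months, here 1 − e^−0.02 = 1.98%. The incidence with death as a competing event is:

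- d = 0.05: 0.02/0.07 × (1 − e^−0.07) = 1.93%; overstated by 2.5% relative, 0.05 percentage point.
- d = 0.1054, which gives 10% mortality at 1 year because 1 − e^−0.1054 = 0.10: 1.88%; overstated by 5.3% relative, 0.10 percentage point.

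If the 10% is read as 12-month mortality, the second line is about the largest error that the rule allows at these rates.

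**The case against.** Several counter-arguments carry weight.

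- **Place in the study.** The primary objectives estimate risk by treatment, and the person-year incidence rates do not depend on the regression model. The comparisons are a secondary objective. This stands, and it lowers the severity.
- **Safeguards already planned.** Unadjusted rates per 100 person-years, all-cause mortality by drug and compared between drugs, and causes of censoring by group will all be reported. A careful reader could see whether a Fine-Gray difference follows a mortality difference. This stands in part: it helps to interpret a mortality-driven ratio, but the ratio would still be the reported result.
- **Propensity adjustment.** Adjustment or matching should narrow the mortality gap between arms, so 5 vs 12 per 100 person-years is an extreme case. This stands.
- **The two statements can be reconciled.** Section 3.4.2 can be read as Cox by default with Fine-Gray as a contingency, and the 10% in section 3.4.1 may be what is meant by high. That is possible, but the text does not link them, and a contingency based on mortality still changes the quantity estimated. That the article gives no horizon or population for the 10% is not counted against it, since the full protocol may state them.
- **Fine-Gray is a valid method.** It is, for absolute risk. The fault lies in substituting it for Cox in a comparison of drug effects because deaths were frequent.

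A reader might infer that the model will be picked to suit the stroke or bleeding result, or that the three apixaban comparisons will end up on different scales. The document supports neither. The trigger is mortality, its direction is stated beforehand, and section 3.4.2 speaks of one final choice of model.

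**Conclusion.** The point holds as a should-fix. The document states a rule by which observed deaths select the quantity estimated in the comparisons, next to a statement that Cox was chosen in advance. It also states a threshold for the curves that its own reasoning does not support. Nothing elsewhere in the article repairs either rule.

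The likely size is small. If Fine-Gray is triggered, the spurious ratio is about 1.01 to 1.06 under staggered entry and stopping, depending on the mortality gap; if Cox is used, it is nil. The upper figure of 1.11 needs a 2.4-fold difference in death rates and three full years of follow-up for everyone. The error in the 12-month curves is about 0.05 to 0.10 percentage point. All of this rests on assumed constant rates, because the article gives none. It would be too strong to conclude that the comparisons will be seriously biased or that the primary incidence rates are affected. A ratio of 1.05 would need about 4 × (1.96 + 0.84)² / (ln 1.05)² ≈ 13,200 events for 80% power, and the article gives no event count to compare with this.

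**What to change.** 1. In section 3.4.1, use the cumulative incidence estimator with death as a competing event for all curves, whatever the mortality, and delete the 10% condition.
2. In section 3.4.2, name the cause-specific Cox model, with deaths censored, as the main comparative model for stroke/systemic embolism and for major bleeding. This agrees with the stated comparability aim. Delete the mortality-based trigger.
3. Report Fine-Gray as a supplement for each comparison, beside the all-cause mortality hazard ratio that is already planned.

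The cost is a change of wording and one supplementary model per comparison and outcome, because the plan now uses one model or the other, not both. No new data are needed.
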